# Does the use of higher versus lower oxygen concentration improve neurodevelopmental outcomes at 18–24 months in very low birthweight infants?

**DOI:** 10.1186/s13063-024-08080-2

**Published:** 2024-04-04

**Keywords:** Infant, Extremely preterm, Neonatal intensive care, Delivery room, Oxygen, Neonatal mortality

## Abstract

**Background:**

Immediately after birth, the oxygen saturation is between 30 and 50%, which then increases to 85–95% within the first 10 min. Over the last 10 years, recommendations regarding the ideal level of the initial fraction of inspired oxygen (FiO_2_) for resuscitation in preterm infants have changed from 1.0, to room air to low levels of oxygen (< 0.3), up to moderate concentrations (0.3–0.65). This leaves clinicians in a challenging position, and a large multi-center international trial of sufficient sample size that is powered to look at safety outcomes such as mortality and adverse neurodevelopmental outcomes is required to provide the necessary evidence to guide clinical practice with confidence.

**Methods:**

An international cluster, cross-over randomized trial of initial FiO_2_ of 0.3 or 0.6 during neonatal resuscitation in preterm infants at birth to increase survival free of major neurodevelopmental outcomes at 18 and 24 months corrected age will be conducted. Preterm infants born between 23^0/7^ and 28^6/7^ weeks’ gestation will be eligible. Each participating hospital will be randomized to either an initial FiO_2_ concentration of either 0.3 or 0.6 to recruit for up to 12 months’ and then crossed over to the other concentration for up to 12 months. The intervention will be initial FiO_2_ of 0.6, and the comparator will be initial FiO_2_ of 0.3 during respiratory support in the delivery room. The sample size will be 1200 preterm infants. This will yield 80% power, assuming a type 1 error of 5% to detect a 25% reduction in relative risk of the primary outcome from 35 to 26.5%. The primary outcome will be a composite of all-cause mortality or the presence of a major neurodevelopmental outcome between 18 and 24 months corrected age. Secondary outcomes will include the components of the primary outcome (death, cerebral palsy, major developmental delay involving cognition, speech, visual, or hearing impairment) in addition to neonatal morbidities (severe brain injury, bronchopulmonary dysplasia; and severe retinopathy of prematurity).

**Discussion:**

The use of supplementary oxygen may be crucial but also potentially detrimental to preterm infants at birth. The HiLo trial is powered for the primary outcome and will address gaps in the evidence due to its pragmatic and inclusive design, targeting all extremely preterm infants. Should 60% initial oxygen concertation increase survival free of major neurodevelopmental outcomes at 18–24 months corrected age, without severe adverse effects, this readily available intervention could be introduced immediately into clinical practice.

**Trial registration:**

The trial was registered on January 31, 2019, at ClinicalTrials.gov with the Identifier: NCT03825835.

**Supplementary Information:**

The online version contains supplementary material available at 10.1186/s13063-024-08080-2.

## Introduction

### Background and rationale {6a}

#### Normal oxygen transition at birth

At birth, the oxygen saturation (SpO_2_) is around 30% [1], which then increases over the next 7–10 min to values of 85–95% [2]. The goal of a successful resuscitation for extremely low birth weight (ELBW) infants is to facilitate transition from intrauterine SpO_2_ levels to the accepted post-transitional neonatal range using simple SpO_2_ targets [3, 4].

#### Concerns for oxygen toxicity and deficit

The use of supplementary oxygen may be crucial but also potentially detrimental to preterm infants at birth. High oxygen levels may lead to organ damage through oxidative stress, while low oxygen levels may lead to increased mortality. Excess of oxygen free radicals in infants intrinsically deficient in enzymatic antioxidants and non-enzymatic antioxidants may contribute to these morbidities. Pulmonary oxygen toxicity, through the generation of reactive oxygen and nitrogen species in excess of antioxidant defenses, is believed to be a major contributor to the development of bronchopulmonary dysplasia (BPD) [5–10]. Varsila et al. noted that immaturity is the most important factor explaining free radical-mediated pulmonary protein oxidation in ELBW infants and that oxidation of proteins is related to the development of BPD [11]. Using lower oxygen concentrations at birth results in decreased oxidative stress markers and decreased risk of developing BPD compared to higher oxygen concentrations [12]. Other organs that may be damaged by such oxidative stress include kidneys, myocardium, and the retina [13–16].

#### The current International Liaison Committee on Resuscitation (ILCOR) guidelines

In 2010, ILCOR guidelines were revised to recommend that air or “less oxygen” should be used initially for preterm infants [17, 18] and that oxygen concentrations should be adjusted during resuscitation to meet SpO_2_ ranges that were similar to those of spontaneously breathing, healthy full-term infants [2]. However, the 2015 guidelines acknowledged the lack of evidence for either harm or benefit in starting resuscitation with either lower (< 0.3) or higher (> 0.65) FiO_2_ for preterm infants (i.e., < 37 weeks’ gestation) [19, 20] as well as the need for further research into establishing appropriate time-specific oxygen targets and to determine neurodevelopmental consequences of this practice in preterm infants. Indeed, a recent survey of 630 clinicians from 25 countries showed that the majority would initiate preterm infant delivery room stabilization with 0.30–0.4 initial FiO_2_ [21].

#### Summary of current evidence

Randomized controlled trials evaluating different oxygen concentrations for resuscitation of preterm infants have been occurring for the past 25 years [10, 22–31]. Furthermore, several systematic reviews highlight the ongoing concern regarding the knowledge gap in this area. Earlier systematic reviews of Brown et al. [32] and Saugstad et al. [33] found a significant (pooled risk ratio (RR) 0.65 [95% confidence interval (CI): 0.43, 0.98]) or borderline significant (relative risk for mortality 0.62 [95% CI: 0.37–1.04]) reduction in mortality when a low (21–50% or 21–30%) compared to a high (> 50% or ≥ 60%) oxygen concentration was used for initial stabilization in preterm infants (≤ 37 or ≤ 32 weeks), respectively. The most recent systematic review by Oei et al. [34] included trials with the same oxygen criteria as Saugstad et al. [33] as well as titration strategies to predefined SpO_2_ targets in preterm infants (≤ 28^+6^ weeks). No differences were found in the overall risk of death with either lower (≤ 30%) or higher (≥ 60%) oxygen concentrations. Collectively, while conclusions for each systematic review differed, all the authors emphasized the need for larger, well-designed trials to provide definitive recommendations for oxygen strategies during preterm delivery room resuscitation.

In a non-pre-specified analysis of the Targeted Oxygen in the Resuscitation of Preterm Infants Trial, infants of < 28 weeks’ gestation who received an initial FiO_2_ of 0.21 at resuscitation had higher hospital mortality than those given an initial FiO_2_ of 1.0 (10/46 [22%] vs. 3/54 [6%]; RR: 3.9 [95% CI: 1.1–13.4]; *p* = 0.01) [23]. Furthermore, the most recent individual patient analysis of eight trials reported that infants who were started with an initial FiO_2_ of < 0.3 had significantly lower 5 min SpO_2_ values compared to infants started with an initial FiO_2_ of ≥ 0.6 [35]. Furthermore, infants initially resuscitated with initial FiO_2_ of 0.21–0.3 compared to initial FiO_2_ of ≥ 0.6 had an increased risk of major intraventricular hemorrhage and a five times higher risk of death [35]. Similarly, if preterm infants resuscitated with initial low FiO_2_ do not reach SpO_2_ of 80% at 5 min, it was associated with increased risk of major intraventricular hemorrhage and an almost five times higher risk of death [35]. There is equally growing evidence that using lower initial FiO_2_ will lead to lower SpO_2_ levels and bradycardia, which may lead to increased rates of mortality in this vulnerable group of infants [34, 36]. These data provide a warning note for the use of higher vs. lower initial FiO_2_ during delivery room resuscitation. Trials are urgently needed to evaluate the risk of using low and high initial FiO_2_ in preterm infant stabilization at birth [37]. In summary, the “optimal” FiO_2_ used to initiate post birth stabilization of extreme preterm seems to be about balancing the need to quickly achieve target saturations while minimizing the oxidative stress of “too much” oxygen.

## Objectives {7}

### Primary research question

The trial is based on the following Population (P), Intervention (I), Comparison (C), Outcome (O), Timeline (T) format: (*P*) in preterm infants born at 23^0^–28^6^ weeks’ gestation, (*I*) does initiating resuscitation with an initial FiO_2_ of 0.6 (*C*) compared to initiating with an initial FiO_2_ of 0.3 (*O*) increase or decrease the incidence of mortality or the presence of major neurodevelopmental outcomes as defined: (i) cerebral palsy with an inability to walk unassisted; (ii) major developmental delay involving cognition or speech, (iii) visual (cannot fixate/legally blind, or corrected acuity < 6/60 in both eyes), or hearing impairment (requiring a hearing aid or cochlear implants) (*T*) at 18–24 months corrected age?

### Secondary objectives

In preterm infants born at 23^0^–28^6^ weeks of gestation, does initiating resuscitation with a higher initial FiO_2_ of 0.6 compared to a lower initial FiO_2_ of 0.3 increase or decrease the components of the primary outcome (death, cerebral palsy, major developmental delay involving cognition, speech, visual, or hearing impairment) in addition to neonatal morbidities (severe brain injury, bronchopulmonary dysplasia; and severe retinopathy of prematurity)?

### Trial design {8}

This is an international, multicenter, cluster, cross-over, superiority randomized controlled trial.

## Methods: participants, interventions, outcomes

### Study setting {9}

The study setting is as follows: delivery rooms of tertiary level perinatal centers in Canada, Ireland, and Spain. All recruiting sites have been entered into ClinicalTrials.gov (https://clinicaltrials.gov/study/NCT03825835) and attached as Appendix.

### Eligibility criteria {10}

Inclusion criteria (all must be satisfied):Born between 230/7 and 286/7 weeks’ gestation.To receive full resuscitation, i.e., no parental request or pre-determined decision to forego resuscitation.No known major congenital or chromosomal malformation.Informed parental consent.

### Exclusion criteria

Infants who are born outside of study center and transported to center after delivery.Parental refusal or could not be approached for consent.

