### Consent or assent: who will take informed consent? {26a}

Informed parental/guardian consent will be obtained after the study intervention for ongoing data collection and follow-up research staff trained to obtain consent for the trial as per Tri-Council Policy Statement: Ethical Conduct for Research Involving Humans guidelines for research in “Individual Medical Emergencies” [38].

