### Duration of treatment period

The study intervention duration will be the first 10 min after birth.

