## Participant timeline {13}

**Table Taba:** 

	**Enrolment**	**Allocation**	**Post-allocation**		**Post-discharge**
**Time point**	Antenatal	At birth	7–10 days of age	Hospital discharge	24 ± 6 months’ (corrected for prematurity)

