### Recruitment {15}

All centers were carefully selected as they have previously participated in large randomized trials and have the documented capability of enrolling the required number of infants. All participating centers will change their local hospital policy to either 30 or 60% oxygen as per randomization for the first cohort of infants. As units will switch their policy of initial oxygen concentration for the study period, it is very unlikely that non-compliance will be an issue; however, we will monitor and record carefully. This approach allows all infants born at each center, being automatically included in the trial. The consent approach for the HiLo trial will be unambiguous and acceptable for all participating centers by obtaining individual consent after birth for data inclusion in the trial and follow-up, which will strengths the number being recruited.

The number of infants being recruited will vary between 10 and 70/year depending in the size of the center. The overall recruitment period is a max of 24 months per center; however, if a center reaches their target for the first arm prior of 12 months, the center will switch to the 2nd arm. We estimate ~ 1120 infants being recruited in Canada, ~ 60 infants in Ireland, and ~ 120 infants in Spain.

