### Adverse event reporting and harms {22}

Safety reporting from the HiLo trial will follow standards from Health Canada as per section C.05.014 of the Food and Drug Regulations and the Tri-Council Policy Statement: Ethical Conduct for Research Involving Humans [38].

Pre-defined SAE are as follows:Death in the delivery room (also a component of the primary outcome)Death in the NICU (also a component of the primary outcome)Intraventricular hemorrhage grade 3 or higher according to Papile [44]

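### Consent taken after treatment is a condition of eligibility, so the printed criteria allow outcome-dependent exclusion and conflict with automatic inclusion and intention-to-treat

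*Protocol article*

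**What the plan says.** All references are to the Protocol article.

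- **Eligibility criteria {10}**: all inclusion criteria must be met, and one of them is "Informed parental consent".
- **Exclusion criteria**: "Parental refusal or could not be approached for consent".
- **Duration of treatment period**: "The study intervention duration will be the first 10 min after birth".
- **Consent or assent {26a}**: "Informed parental/guardian consent will be obtained after the study intervention for ongoing data collection and follow-up", under the cited guidelines for research in medical emergencies.
- **Participant timeline {13}**: the informed-consent row is marked in the column headed "7–10 days of age" and in the hospital-discharge column.
- **Recruitment {15}**: "This approach allows all infants born at each center, being automatically included in the trial". The same paragraph describes individual consent after birth as consent for a child's data to be included.
- **Implementation {16c}**: staff who know the allocation enrol every participant automatically.
- **Who will be blinded {17a}**: only the neurodevelopmental assessors are blinded.
- **Statistical methods {20a}**: the primary analysis is by intention to treat.
- **Primary outcome** and **Analysis population and missing data {20c}**: publishing in-hospital mortality and severe brain injury first is said to secure nearly complete ascertainment.
- **Adverse event reporting and harms {22}**: death in the NICU is a pre-defined serious event and counts in the primary outcome, and so does "Death in the delivery room (also a component of the primary outcome".

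**The concern.** Under these criteria, membership of the trial is settled after treatment, by events that treatment may influence. Parents of an infant who dies in the delivery room or soon after may be harder to approach than parents of a survivor. If they are not approached, the infant meets an exclusion criterion and fails an inclusion criterion, yet the same death is an event in the primary outcome. Sites know the arm throughout, so both approach and refusal could differ between arms.

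Death makes up 18 of the 35 percentage points expected for the composite (Sample size {14}), so the rule bears on about half of the expected events, and on in-hospital mortality, which is to be published first. The planned remedies do not reach it. Multiple imputation fills in missing values for trial participants, not for infants ruled ineligible. Adjustment for gestational age cannot restore deaths that are not in the data set.

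**Working it through.** **Step 1. Can the statements all hold?** Take an eligible infant who is resuscitated under the allocated policy and dies before a parent is approached.

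| Section | Consequence for this infant |
|---|---|
| Eligibility criteria {10} | Not included: no consent |
| Exclusion criteria | Excluded: not approached |
| Recruitment {15}, Implementation {16c} | Included automatically |
| Statistical methods {20a} | Analysed by intention to treat |
| Adverse event reporting {22} | A primary-outcome event |

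The first two rows contradict the last three. The only other data provision, under Consent or assent: ancillary studies {26b}, covers participants who later withdraw.

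**Step 2. Reproduce the planned sample size.** Inputs from the Abstract and Sample size {14}: 35% against 26.5%, 5% type I error (taken as two-sided), 80% power, ICCs 0.034 and 0.029, up to 20 centers, 10% loss.

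- Mean cluster-period size: 1200 / (20 × 2) = 30.
- Design effect: 1 + (30 − 1) × 0.034 − 30 × 0.029 = 1.116.
- Two proportions: 462 per arm; × 1.116 gives 516; / 0.90 gives 574; total 1148.
- With continuity correction: 485, then 542, then 603 per arm; total 1206, against 1200 stated.

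The plan's figure is reproduced to within normal choices of formula. The issue is selection, not sample-size arithmetic.

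**Step 3. Baseline power.** Evaluable per arm: 600 × 0.90 = 540. Effective n = 540 / 1.116 = 483.9. An exact 25% reduction takes 35% to 26.25%. With mean rate 0.30625:

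- SE under the null: √(2 × 0.30625 × 0.69375 / 483.9) = 0.0296.
- SE under the alternative: √((0.35 × 0.65 + 0.2625 × 0.7375) / 483.9) = 0.0295.
- (0.0875 − 1.96 × 0.0296) / 0.0295 ≈ 1.00, so power is 84.1% (81.8% at 26.5%).

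**Step 4. Equal loss in both arms.** Let d be the death rate, i the impairment rate and f the share of deaths excluded. The article gives no f; the range 10% to 50% is an assumption. The observed composite is

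(d(1 − f) + i) / (1 − d·f).

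Control arm: d = 0.18, i = 0.17. At f = 0.30: (0.126 + 0.17) / (1 − 0.054) = 0.296 / 0.946 = 31.29%.

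Two assumed true effects: (A) both components fall by 25% (d = 0.135, i = 0.1275); (B) all 8.75 points are in mortality (d = 0.0925, i = 0.17). Evaluable numbers are held at 540 per arm, so only the change in rates counts.

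| f | Control deaths lost per 600 (of 108) | Control composite, % | Control mortality, % | A: rate / difference / power | B: rate / difference / power |
|---|---|---|---|---|---|
| 0 | 0 | 35.00 | 18.0 | 26.25 / 8.75 / 84.1% | 26.25 / 8.75 / 84.1% |
| 10% | 11 | 33.81 | 16.5 | 25.24 / 8.57 / 83.3% | 25.56 / 8.25 / 80.3% |
| 20% | 22 | 32.57 | 14.9 | 24.20 / 8.37 / 82.4% | 24.86 / 7.71 / 75.6% |
| 30% | 32 | 31.29 | 13.3 | 23.14 / 8.15 / 81.4% | 24.15 / 7.14 / 70.0% |
| 50% | 54 | 28.57 | 9.9 | 20.91 / 7.66 / 78.9% | 22.67 / 5.90 / 55.6% |

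**Step 5. No true effect, unequal loss.**

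- 10% against 20%: 33.81% against 32.57%, a spurious 1.2 points; two-sided rejection about 7%.
- 10% against 30%: 33.81% against 31.29%, a spurious 2.5 points. SE = √(2 × 0.3255 × 0.6745 / 483.9) = 0.0301; shift = 0.0252 / 0.0301 = 0.84; rejection = 1 − Φ(1.96 − 0.84) + Φ(−1.96 − 0.84) ≈ 13%.

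Equal loss with no true effect creates no difference between arms.

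**The case against.** A reader might infer that the trial discards every delivery-room and first-week death and that the primary result is therefore biased. The documents do not support that.

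- No sentence says that early deaths are dropped. Bereaved parents can be approached, and {26a} requires only that consent follow the intervention.
- The timeline has no column between birth and 7–10 days. Consent taken on days 0 to 6 has nowhere else to be marked, so the table does not show that consent waits until day 7.
- The timeline marks assessment of in-hospital mortality from birth onward, and {22} makes delivery-room and NICU deaths reportable. This suggests that deaths are recorded for safety, so bias in the safety board's interim looks is not shown either.
- The rationale speaks of hospital mortality, hemorrhage and risk of death. It does not say that the benefit is expected in early deaths.
- With equal loss and a proportional effect on both components, the cost is small (column A).
- Excluding infants whose parents actively refuse may be an ethical requirement, and the full protocol or manual of operation may say how deceased infants are handled.

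All of this limits how much harm can be claimed. It does not remove the conflict. Recording a death for safety does not place the infant in the analysis set when the eligibility criteria exclude that infant and Recruitment {15} ties consent to data inclusion. The criteria are stated text, not detail left out of a condensed article.

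**Conclusion.** The point stands as a contradiction in the printed plan: the consent criteria permit exclusion that depends on the outcome, and they cannot be squared with automatic inclusion, intention to treat, near-complete ascertainment, or delivery-room death as a primary-outcome event.

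Whether bias will arise, how large, and in which direction cannot be known from the article. The consequences range from slight to serious. With equal loss of 10–50% of deaths, power moves from about 84% to 83–79% (proportional effect) or to 80–56% (effect wholly on mortality), and observed control mortality is understated at 16.5% to 9.9% instead of 18%. A false effect under the null needs unequal loss: about 7% rejection at 10% against 20%, about 13% at 10% against 30%. Unequal loss is possible because sites are not blinded, but nothing in the article shows that it occurs. Every loss fraction is an assumption, as are the mean cluster-period size of 30 and the fixed 540 evaluable infants per arm.

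**What to change.** 1. Remove failure to approach from the exclusion criteria. In Eligibility criteria {10}, recast the consent item as consent to further data collection and to follow-up. Changing the exclusion alone would leave unconsented infants ineligible under {10}.
2. Define the intention-to-treat set as all eligible inborn infants managed during the allocated policy period, except where a parent refuses use of the data. Align {10}, the exclusions and {26a} with {15}, {16c}, {20a} and {22}.
3. Where ethics boards permit, use a waiver or alteration of consent for a minimal de-identified record on infants who die or are not approached: center, period and arm, gestation, sex, in-hospital death, severe hemorrhage. Elsewhere, collect aggregate counts.
4. Report refusals and unapproached infants by arm, period and, where permitted, vital status.
5. Add a bounding sensitivity analysis for the primary outcome and in-hospital mortality: known deaths counted as events, and unknown outcomes set to the extremes favoring each arm in turn.

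**Cost.** An ethics amendment at sites in three countries and a short data form; no extra patients. Recruitment began in June 2022, so infants already recruited may have to be handled differently from later ones, and the report should say so. Some boards may allow only aggregate counts, which leaves the bounding analysis wider for those centers.

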### Consent or assent: who will take informed consent? {26a}

Informed parental/guardian consent will be obtained after the study intervention for ongoing data collection and follow-up research staff trained to obtain consent for the trial as per Tri-Council Policy Statement: Ethical Conduct for Research Involving Humans guidelines for research in “Individual Medical Emergencies” [38].

